## Abstract

Access to secondary psychiatric consultation is often challenging for general practitioners (GPs), potentially resulting in treatment delays or increased reliance on emergency services. The *med@psy* system is a collaborative care platform that enables GPs to schedule consultation appointments with psychiatrists within 48 hours. This study aims to compare the implementation of outpatient follow-up between two care pathways: attendance at a psychiatric emergency department for a consultation followed by discharge home and psychiatric consultation referred by the patient’s GP via the *med@psy* collaborative care system. The study consists of two prospective, multicenter, comparative and nonrandomized cohorts. Patients will be teleconsulted at one month and again at three months to assess whether they have received appropriate outpatient follow-up. This is a real-life study involving GPs and psychiatrists within a collaborative care model. The strengths and limitations of this study are discussed below. The results of this study will help gather valuable data on these two care pathways and will serve as a basis for improving and optimizing patient management strategies in outpatient mental health care.

Trial registration

ClinicalTrials.gov NCT06581874

## Introduction

Access to care and unscheduled care are major public health concerns. The problem is even more significant in psychiatry, where the COVID-19 pandemic has further increased the demand for care in an already overburdened system. According to the French COVID-19REV survey (wave 37) conducted in September 2023, 23% of respondents reported signs of anxiety, and 16% reported signs of depression [1]. A significant proportion of these situations (25%), known as mild or moderate disorders, can be managed in primary care if general practitioners (GPs) have access to psychiatric referrals [2].

General practitioners (GPs) are the primary point of contact for mental health services in France and numerous countries [3]. They play a strategic role in the coordination and management of psychiatric disorders [4,5]. The coordinated care pathway is separated into two referral levels: primary care, centered around GPs, who are responsible for patient referral, and secondary care, which is provided by specialists and health establishments [6] and is intended for cases requiring more complex interventions. The deployment of earlier and more graduated care has the advantage of reducing the intensity of psychiatric disorders and their repercussions [7]. Initial consultation with psychiatrists should take place as early as possible. However, this hierarchical model has limitations. Access to second-line psychiatric care can be difficult, leading to treatment delays or referrals to an unsuitable care pathway. Psychiatric emergency departments are becoming the gateway to psychiatric care. This trend is accompanied by an increase in emergency visits, including a growing number of “inappropriate or avoidable visits” [8].

Cooperation between GPs and psychiatrists is therefore essential. The collaborative care model facilitates this cooperation. Collaborative mental health care can be defined as *the process in which primary care and mental health professionals share resources, expertise, knowledge and decision-making to ensure that primary care populations receive care that is person-centered, effective, efficient and delivered by the appropriate professional* [9]. Recommendations for the mental health field have already been formalized [10].

Analysis of the issues described above led to the development of the *med@psy* system, supported by the digital platform *med@med.* This is an innovative collaborative care system in the mental health care pathway. The *med@psy* system combines human (telephone support) and digital logistical support to help GPs address the difficulties and isolation they often face when dealing with psychiatric cases in daily practice. GPs use this system to guide their patients toward the most appropriate care pathway, with step-by-step assistance provided by a medical decision support system. Fig 1 shows how the *med@psy* system works. The *med@psy* system encourages organization and collaboration between GPs and psychiatrists. It supports the implementation of primary mental health care by facilitating timely access to specialist input. This allows GPs to obtain real-time secondary psychiatric consultations within 48 hours through a shared care model, enhancing coordinated patient management and continuity of care.

**Fig 1 pone.0343295.g001:**
[figure not shown]
Description of the *med@psy* system user circuit.

Three main categories of psychiatric clinical conditions can lead to consultations at the emergency department: “pure” psychiatric emergencies (acute decompensation of a characterized psychiatric condition), “mixed” emergencies (involving both psychiatric and nonpsychiatric symptoms) and “transient acute states” (intense emotional reactions) [11]. The *med@psy* system mainly addresses acute transient states in which there is no immediate risk of action, such as suicide attempts. It can also address prodromal states or symptomatic exacerbations in patients with an established psychiatric disorder who are being followed by a general practitioner.

The system has been specifically set up at Métropole Toulon Provence Méditerranée. In 2018, this urban area had a population of 438,985 for 366.41 km^2^, with 83 psychiatrists and 436 GPs. Within this territory, between 1 July 2021 and 30 June 2022, 1460 psychiatric consultations were conducted in the psychiatric emergency unit of the Toulon – La Seyne-sur-Mer Intercommunal Hospital Center (CTS), with patients discharged home without hospitalization. Among these patients, 80% required outpatient follow-up (n = 1168), and it was estimated that only 10% of patients received follow-up one month later. The *med@psy* system differs from existing systems in other French regions because it is based on a single-entry point through GPs. It takes advantage of existing networks (both hospital and private practices) by stimulating them to optimize the link between GPs and psychiatrists. Its advantages include ease of use, digital efficiency and support for medical decision-making, allowing a tailored response to the patient’s need to be proposed in less than five minutes. The system promotes patient involvement and ensures that the time between the GP’s request and the patient’s appointment validation is under two hours. The system facilitates the scheduling of appointments within 48 hours of referral. It operates through a stepped referral process: initially, a personalized referral to a specific psychiatrist is made; if the psychiatrist is unavailable, the referral is voluntarily extended to the entire network, and in cases of no response, it is automatically redirected to other psychiatric network resources to ensure timely care. Furthermore, the coordination efforts of both the general practitioner and the psychiatrist are acknowledged through increased reimbursement for consultations.

### Aim

We hypothesize that the *med@psy* system, which enables patients to obtain a psychiatric consultation within 48 hours of referral from a general practitioner, facilitates the rapid implementation of outpatient follow-up. This study aims to compare the implementation of outpatient follow-up between two care pathways: one visit to the psychiatric emergency department with the patient discharged home without hospitalization and one psychiatrist consultation via the *med@psy* system following referral by the patient’s GP.

## Materials and methods

### Study design

This study is designed as a prospective, multicenter, nonrandomized comparative cohort study involving two distinct groups: Group 1 and Group 2. Group 1 consisted of patients who presented to the emergency department of the Toulon-La Seyne-sur-Mer Intercommunal Hospital Center (CTS) regardless of whether they were referred by their GP. Group 2 consisted of patients referred by their GP for a psychiatric consultation through the *med@psy* system. Patients will be selected and included from two investigating centers: the *med@psy* system, which is attached to psychiatric practice, and the CTS Emergency Department.

### Procedure

All patients meeting the eligibility criteria will be identified following their consultation, either at the CTS psychiatric emergency department with an outpatient discharge (Group 1) or following referral by their GP for a psychiatric consultation scheduled within 48 hours *via* the *med@psy* system (Group 2).

Prior to any examination or research-related procedure, the investigator will obtain the patient’s non-opposition of the person undergoing the research. The identified patients will be contacted by telephone by the investigator or a member of the team to be informed about the research. The information will be given both orally and in writing, using a non-opposition information note. It will be written in clear language that the patient can fully understand. Patients will be given sufficient time to consider their participation. The enrollment, intervention, and assessment schedules are presented in Fig 2 and the study flowchart is shown in Fig 3.

**Fig 2 pone.0343295.g002:**
[figure not shown]
Schedule of enrollment, interventions, and assessments.

**Fig 3 pone.0343295.g003:**
[figure not shown]
Description of the study process. (GAF: Global Assessment of Functioning).

For Group 1, after a clinical assessment by a psychiatrist in the emergency department that does not lead to hospitalization, the patient will be given a psychiatric consultation and discharged. The patients were contacted within one week of their visit to the emergency department to be informed about the research. If the patient does not object to participation, they will be contacted at one month and three months post-visit by a psychologist, who will administer the Global Assessment of Functioning (GAF) scale and collect information regarding any follow-up with a psychologist, psychiatrist or general practitioner.

For Group 2, patients will be seen within 48 hours of consulting their GP by a psychiatrist taking part in the *med@psy* system. As part of the research, patients will be contacted within a week of this consultation to be informed about the research. If the patient does not object to participation, they will be contacted at one month and three months after their consultation via the application by the study psychologist, who will administer the GAF scale and collect information regarding any follow-up with a psychologist, psychiatrist or general practitioner.

### Participants sample size

The study will include all patients meeting the inclusion and exclusion criteria over 12 months. Between 1 July 2021 and 30 June 2022, 1460 psychiatric consultations were carried out in the CTS psychiatric emergency department, with patients discharged home without hospitalization. If 80% of these patients are estimated to require outpatient follow-up, this corresponds to 1168 patients.

Based on preliminary estimates, 10% of patients seen in the emergency departments (Group 1) are expected to have outpatient follow-up set up at one month, compared with 20% of patients seen *via* the *med@psy* system (Group 2). Considering the null hypothesis as the equality of two proportions, with a first order risk (alpha) of 5%, the simple size calculation using the SAS (*Statistical Analysis Software*) power procedure estimates that a total of 434 patients are required (217 per group) to detect a statistically significant difference with a power of at least 90%. When a 10% drop-out rate is allowed, a minimum of 239 patients per group should be included, which seems plausible over a 12-month inclusion period.

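### The stated minimum of 239 per group does not leave the required 217 after 10% drop-out; 217/0.90 gives 242.

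*Protocol article*

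**What the plan says.** Everything needed is in the protocol article, section Participants sample size. For the emergency pathway the planning assumption is "10% of patients seen in the emergency departments (Group 1) are expected to have outpatient follow-up set up at one month". For the med@psy pathway the assumed proportion at the same time point is 20%. The hypothesis is given as "Considering the null hypothesis as the equality of two proportions" and the error rate as "with a first order risk (alpha) of 5"%, but nothing says whether the test is one-sided or two-sided. The result is "a total of 434 patients are required (217 per group"), and the purpose is "to detect a statistically significant difference with a power of at least 90"%.

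The drop-out step follows: "When a 10% drop-out rate is allowed, a minimum of 239 patients per group should be included". No inflation formula is shown. The same section opens with the recruitment rule: "The study will include all patients meeting the inclusion and exclusion criteria over 12 months".

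**The concern.** The section gives a required number (217), a loss rate (10%) and a number to include (239). The number to include should be large enough that the required number is still there after the loss, and 239 is not.

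The loss is a loss of primary-outcome data. Under Outcomes, one-month follow-up status is collected from the patient at the one-month teleconsultation, so a patient who cannot be reached then has no recorded primary outcome. The 10% also naturally applies to patients included, because the sentence sets how many to include. That calls for dividing by 0.90, not multiplying by 1.10.

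Little is at stake in patient numbers, but the article presents 239 as a minimum attached to a power claim of at least 90%. It is the natural yardstick for whether recruitment was sufficient. It could matter most for Group 2, because the Discussion names low uptake by GPs as a risk to recruitment.

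**Working it through.** **Inputs** (all from Participants sample size): p1 = 0.10, p2 = 0.20, alpha = 0.05 (sidedness not stated), power at least 0.90, 217 per group with equal allocation, drop-out 10%, stated minimum 239 per group.

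**1. Reproduce 217.** Pooled-variance normal approximation, no continuity correction:

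n = [z(alpha)·√(2·p̄·(1−p̄)) + z(power)·√(p1(1−p1) + p2(1−p2))]² / (p2−p1)²

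with p̄ = 0.15, √(2 × 0.15 × 0.85) = 0.505 and √(0.09 + 0.16) = 0.5.

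- One-sided 5%: (1.645 × 0.505 + 1.282 × 0.5)² / 0.01 = 216.5, so **217**, an exact match.
- Two-sided 5%: (1.960 × 0.505 + 1.282 × 0.5)² / 0.01 = 265.9, so 266, which does not match.

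**2. Reproduce 239.** 217 × 1.10 = 238.7, so **239**, an exact match. The article shows no formula, so this route is inferred.

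**3. Test 239 against the plan's own requirement.**

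- Evaluable after 10% loss: 239 × 0.90 = 215.1, below 217.
- Largest loss that 239 can absorb: 1 − 217/239 = 9.2%, below 10%.

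This step needs only the article's own figures and does not depend on how 239 was obtained.

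**4. Correct inflation.** 217 / (1 − 0.10) = 241.1, so **242 per group**, 484 in total, against 2 × 239 = 478. Check: 242 × 0.90 = 217.8, which is enough; 241 × 0.90 = 216.9, which is just short.

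**5. Effect on power**, p1 = 0.10 against p2 = 0.20:

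| Evaluable per group | One-sided 5%, normal approximation | One-sided 5%, exact binomial | Two-sided 5%, normal approximation |
|---|---|---|---|
| 217 | 90.06% | 90.65% | 83.32% |
| 215 | 89.82% | 90.39% | 82.97% |

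The exact binomial column is the power of the same pooled z-test, summed over all possible outcomes. Under the approximation that yields 217, the 90% threshold is met at 217 and narrowly missed at 215. Under exact enumeration both sizes stay above 90%.

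**6. If the base size becomes 266 (two-sided).** 266/0.90 = 295.6, so 296 per group; multiplying instead would give 266 × 1.10 = 292.6, so 293. The same slip would again leave the total three per group short.

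**The case against.** The strongest reply is that nothing in enrolment turns on this number. All eligible patients are taken over a fixed 12-month window, 239 is a floor used to argue feasibility, and the article attaches no stopping rule or action to it. The difference is 3 inclusions per group (3/239 = 1.3%) and about 0.2 points of power, with both values rounding to 90%. The 10% rate is itself a round assumption with no source given, and 239 still covers a loss of 9.2%. All of this stands, and it is why the point is minor.

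Three further remarks also have force. The multiplication by 1.10 is a back-calculation, not something the article states. The 89.8% figure depends on a one-sided test that the article never declares, and on the normal approximation. And 242 is only as good as the 217 beneath it: under a two-sided 5% test, power is already about 83% at 217, beside which two patients hardly count.

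None of this makes 239 consistent with 217 and 10%. Nor is it a matter of an article leaving detail to a fuller document: the article prints a figure that disagrees with the two figures beside it.

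**Conclusion.** The concern holds as a minor arithmetic error. On the article's own figures, the stated minimum leaves about 215 evaluable patients per group where 217 are required. The shortfall is about 2 per group in evaluable patients, or 3 per group (6 in total) in inclusions.

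This conclusion assumes that the 10% applies to patients included and that a drop-out has no one-month outcome. The statement that power slips just below 90% rests on more: a one-sided 5% test and the normal approximation that reproduces 217. The study's ability to answer its question is not materially affected by this slip alone. The undeclared one-sided basis of the 217 is a separate and larger matter.

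**What to change.** In Participants sample size, replace 239 with 242 per group and give the total as 484. Alternatively, keep 239, say that it leaves about 215 evaluable per group at 10% drop-out, and restate the power for that number. Showing the formula, required number divided by (1 − drop-out rate), would prevent a repeat.

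Make the change after the sidedness of the primary test has been settled. If the 217 stands on a declared one-sided 5% test, the minimum is 242; if the test is two-sided at 5%, the base is 266 and the minimum is 296 per group.

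For the drop-out correction itself, the cost is one figure in one sentence. Enrolment already takes all eligible patients over 12 months, so no recruitment rule changes.

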### Inclusion and exclusion criteria

The inclusion criteria were as follows: (1) patients aged 18 years or older; (2) patients presenting to the CTS psychiatric emergency department, with or without referral, who received a psychiatric consultation and were discharged home without hospitalization after clinical evaluation (Group 1) or who were referred for psychiatric consultation *via* the *med@psy* system (Group 2); and (3) patients with indications for outpatient follow-up. (4) Patients with valid social security entitlements.

The exclusion criteria were as follows: (1) patient opposition to participate in the research and (2) patient was currently under psychiatrist follow-up. Psychiatric follow-up is defined as at least one consultation with a psychiatrist within the past three months, excluding consultations for unscheduled or emergency care; (3) patients referred for a suicide attempt, violent or nonviolent, serious or nonserious; (4) patients with no declared GP; (5) patients already included in the study; (6) patients who do not speak French; (7) patients under judicial protection or safeguard of justice; (8) patients under obligation care, under care order or deprived of liberty; and (9) any other reason that, in the investigator’s opinion, could interfere with the evaluation of the study objectives.

### Outcomes

The main objective of this study was to compare the proportion of patients with a psychiatric disorder who received outpatient follow-up one month after a visit to a psychiatric emergency department without hospitalization (Group 1), *versus* one month after a psychiatrist consultation conducted within 48 hours *via* the *med@psy*
*medical* system (Group 2). The primary outcome is the presence or absence of outpatient follow-up, which is defined as at least one consultation with a psychiatrist (excluding psychiatric consultations at the emergency department or psychiatric consultations *via* the *med@psy* system), a psychologist or a general practitioner. Only GP consultations specifically related to psychiatric reasons were considered. This information will be collected during the teleconsultation visit with the psychiatrist at one month. The one-month follow-up period begins from the date of the psychiatric consultation *via*
*either* the *med@psy* system or the CTS emergency department. This timeframe was chosen because it is assumed that there is a delay of approximately three weeks for the implementation of outpatient follow-up for Group 1 patients, which corresponds to the average wait time for the first consultation at the medical-psychological centers in the Métropole Toulon Provence Méditerranée area.

The primary secondary objective was to compare the proportion of patients with a psychiatric disorder who received outpatient follow-up three months after a visit to a psychiatric emergency department without hospitalization (Group 1) *versus* three months after a consultation with a psychiatrist within 48 hours *via* the *med@psy* system (Group 2). As with the primary outcome, outpatient follow-up is defined by at least one consultation with a psychiatrist (excluding emergency department or *med@psy* consultations), a psychologist, or a GP for psychiatric reasons.

The second secondary objective was to compare the overall psychological, social and professional functioning of patients in the two groups via the Global Assessment of Functioning (GAF) scale. The assessment will be conducted by a psychologist during teleconsultations carried out at one and three months. The GAF scale, a component of the Diagnostic and Statistical Manual of Mental Disorders (DSM-IV), provides a global score to subjectively rate the social, occupational, and psychological functioning of an individual. Scores range from 100 (extremely high functioning) to 1 (severely impaired). It incorporates the evaluation of psychological, social, and occupational impairments and considers any physical or social problems that may influence treatment or the severity of the psychiatric condition.

The third secondary objective is to evaluate the adherence of identified medical partners to the use of the *medication* system on the basis of data collected directly from the platform. Adherence will be assessed 12 months after the start of the study: the number of GPs and psychiatrists registered on the *med@psy* system, the number of patients managed *via* the system, the frequency of platform use and the average time between the GP’s referral and the psychiatric consultation provided through the *med@psy* system.

The fourth secondary objective is to characterize the population of patients who received an appointment for a psychiatric consultation within 48 hours *via* the *med@psy* system but who did not attend the scheduled consultation. Patients will be characterized according to the following criteria: age, sex, place of residence, psychiatric diagnosis and reason for referral by the GP.

### Statistics

All collected data will be summarized via descriptive statistics. Categorical variables will be described as frequencies and percentages, whereas continuous variables will be summarized using the median, minimum, maximum and mean (with standard deviation). Comparisons between groups will be conducted via chi² or Wilcoxon‒Mann‒Whitney tests, depending on the nature of the variable, to ensure comparability between groups. Statistical analyses can then be adjusted, and subgroup analyses can be carried out.

The main objective of this study was to compare the proportion of patients in each group who received outpatient follow-up at one month. A Farrington-Manning test will therefore be used to compare these proportions. The first secondary objective will involve a similar comparison of outpatient follow-up at three months between the two groups.

At one and three months, telephone interviews will be conducted by a psychologist to assess the Global Functioning Scale (GAF) score. The distribution of the GAF score between groups will be compared via a nonparametric Wilcoxon Mann‒Whitney test.

At 3 and 12 months, questionnaires will be administered to users of the *med@psy* system (GP and psychiatrists) to assess their overall satisfaction and report any concerns they may have.

System adherence will be assessed 12 months after the start of the study, on the basis of the number of GPs and psychiatrists registered on the platform, the number of patients treated *via* the system, the frequency of use, and the time elapsed between referral and the psychiatric consultation offered *via* the *med@psy* system.

Additionally, the characteristics (age, sex, pathology and reason for referral) of patients who obtained an appointment for a psychiatric consultation within 48 hours via the *med@psy* system but did not attend will be described. These nonincluded patients will have been informed of the research in advance and must not have expressed any opposition to their data being processed. The statistical significance threshold is 5%.

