The *med@psy* system was developed to address difficulties in accessing secondary mental health care, particularly for patients initially managed in primary care. Numerous barriers to the integration of mental health services into the primary care setting have been identified. This includes a low level of interest in mental health care provision among some GPs, increased workload and limited time, insufficient local mental health support, and limited resources for service delivery [12]. However, there are also enablers, such as the ability to understand the patient holistically and the convenience of service provision [12]. This new integrated care pathway via the *med@psy* system responds to facilitators while limiting obstacles. Referral to the platform is simple and takes less than 5 minutes. The *med@psy* system operates on a participatory and voluntary basis. This study highlights the crucial role of psychiatrists in primary care and provides information about the local mental health network. It is advisable to create and maintain up-to-date databases that provide GPs with information about psychiatrist availability, areas of expertise, and modes of practice, as this helps align referrals with appropriate psychiatric services [13]. Timely access to psychiatric consultations helps reduce frustration for both GPs and patients [13]. The *med@psy* system provides information about the various available referrals. Local educational interventions involving secondary care specialists and structured referral forms have also been shown to impact referral rates [14]. In addition, the *med@psy* system integrates reimbursement systems for unscheduled care, thereby enabling its use by GPs and psychiatrists. This approach helps to overcome financial barriers that might impede its implementation [15]. Taken together, these elements represent strong arguments in favor of the adoption and sustained use of the *med@psy* system by GPs.

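### The primary test and sample size assume independent patients although Group 2 shares referring GPs and psychiatrists, so the test may be anti-conservative; add a provider-clustered analysis

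*Protocol article*

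**What the plan says.** **Test.** The Statistics section of the protocol article fixes the primary analysis: "A Farrington-Manning test will therefore be used to compare these proportions". The three-month comparison is to be done in a similar way. Beyond this, the section says only that analyses can be adjusted after the groups have been checked for comparability. No method, covariate or provider term is named.

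**Sample size.** The section on sample size sets up an ordinary two-proportion problem: "Considering the null hypothesis as the equality of two proportions", 10% against 20%, alpha 5% and power of at least 90%. This gives 217 per group, or 239 after a dropout allowance. No design effect or ICC enters.

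**How patients arrive.** Under Study design, "Group 2 consisted of patients referred by their GP for a psychiatric consultation" through the platform. The Introduction explains that a request goes first to one named psychiatrist and is then widened to the network. It describes the area as one "with 83 psychiatrists and 436 GPs". The Discussion adds that the "system operates on a participatory and voluntary basis", and it lists uneven adoption by GPs as a risk.

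**Endpoint.** Under Outcomes, follow-up is at least one consultation with a psychiatrist, a psychologist or a GP. Emergency and platform consultations with a psychiatrist are excluded, and GP visits count when they are for psychiatric reasons.

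**The concern.** With a null difference of zero, the Farrington-Manning test is the pooled score test for two independent binomial samples. Its variance is right only if knowing one patient's outcome says nothing about another's.

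The Group 2 pathway gives reason to doubt that. The GP who referred the patient can personally satisfy the endpoint by seeing the patient again about the same problem. Whether the patient is passed on to a psychologist or another psychiatrist plausibly depends on the consulting psychiatrist's habits and contacts. Participation is voluntary, so a few engaged providers may supply a large share of the group.

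Positive correlation within providers would make the true standard error of the difference larger than the one the test uses. The p-value would then be too small, and any interval built on the same variance too narrow. Because this test carries the main conclusion about the platform, the assumption deserves a check.

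**Working it through.** **Inputs from the article.** Follow-up 10% and 20%; alpha 5%, sidedness not stated; power at least 90%; 217 per group; 83 psychiatrists and 436 GPs in the area.

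**Assumed inputs (not in the article).** ICC 0.01 to 0.10; m = 2 to 20 patients per provider in Group 2. The number of providers using the platform is to be a study result, not a design input.

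**1. The article's own figure.** With pooled variance and no continuity correction,

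n = [z(α)·√(2·0.15·0.85) + z(0.90)·√(0.09 + 0.16)]² / 0.10²

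- One-sided 5%: (1.645·0.505 + 1.282·0.500)² / 0.01 = 216.5, so 217. This matches.
- Two-sided 5%: (1.960·0.505 + 1.282·0.500)² / 0.01 = 265.9, so 266. This does not match; 217 per group gives 83.3% power two-sided.

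The 217 therefore corresponds to a one-sided test of independent patients. Sidedness is a separate matter, so both versions are shown below.

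**2. Plausible cluster sizes for 217 Group 2 patients.**

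- Psychiatrists: 217/83 = 2.6 each if all took part; 217/20 = 10.9 if 20 did; 217/10 = 21.7 if 10 did.
- GPs: 217/100 = 2.2 each if 100 referred; 217/50 = 4.3 if 50 did.

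**3. Effect on the type I error, clustering in Group 2 only.** The design effect is DE = 1 + (m − 1)·ICC. Under the null with equal groups, the test uses variance 2p(1 − p)/n, while the true variance is p(1 − p)(1 + DE)/n. The standard-error ratio is R = √((1 + DE)/2). Actual two-sided alpha is 2·(1 − Φ(1.960/R)); one-sided alpha is 1 − Φ(1.645/R).

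| ICC | m | DE | R | Two-sided | One-sided |
|---|---|---|---|---|---|
| any | 1 | 1.00 | 1.000 | 5.0% | 5.0% |
| 0.01 | 2 | 1.01 | 1.002 | 5.1% | 5.0% |
| 0.02 | 5 | 1.08 | 1.020 | 5.5% | 5.3% |
| 0.05 | 5 | 1.20 | 1.049 | 6.2% | 5.8% |
| 0.05 | 10 | 1.45 | 1.107 | 7.7% | 6.9% |
| 0.10 | 10 | 1.90 | 1.204 | 10.4% | 8.6% |
| 0.05 | 20 | 1.95 | 1.214 | 10.7% | 8.8% |
| 0.10 | 20 | 2.90 | 1.396 | 16.1% | 11.9% |

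**4. What Group 1 adds.** Patients without a declared GP are excluded from both groups, and Group 1 is seen in one emergency department, so Group 1 may be clustered too. Then R = √((DE₁ + DE₂)/2). For example, with ICC 0.02, m = 20 per emergency psychiatrist and m = 5 in Group 2, DE₁ = 1.38, DE₂ = 1.08, R = 1.109 and the two-sided error is 7.7%. In the other direction, a GP with patients in both groups creates positive covariance between the two proportions, which lowers the variance of their difference. The net direction cannot be fixed from the article.

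**5. Effect on sample size.** With the correct standard error, on the one-sided basis that gives 217,

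n = [1.645·√(0.1275·(1 + DE)) + 1.282·√(0.09 + 0.16·DE)]² / 0.10²

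This gives 219 per group for ICC 0.01 and m = 3, 241 for ICC 0.05 and m = 5, 272 for ICC 0.05 and m = 10, and 326 for ICC 0.10 and m = 10.

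**The case against.** A reader might infer that the standard errors are too small and the 5% level is not kept, as a fact. The article does not support that. It gives no ICC, no count of active providers and no patients per provider; with an ICC near zero or one patient per provider, nothing changes. At the GP level, 2 to 5 patients each leaves the error close to nominal. The 16% figure needs 217/20, or about 11 providers, to supply all of Group 2 at ICC 0.10, and nothing in the article says that will happen. These limits stand, and the point is therefore conditional.

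It can also be said that patients are included individually and not allocated by cluster, and that a condensed article commonly leaves variance estimation to an analysis plan that is not shown here. This stands in part: such a plan may contain a provider term. But the article is not silent on the method. It names an independence test for the primary comparison, and its sentence on possible adjustment does not mention providers.

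Finally, robust standard errors and GEE are themselves anti-conservative with few clusters, which is where clustering would matter most. This is correct, so the remedy needs a small-sample correction.

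**Conclusion.** The point holds in conditional form. The primary test and the sample size make no allowance for shared GPs and psychiatrists. The endpoint depends partly on what those providers do, so positive correlation is plausible and the test may be anti-conservative.

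The size depends wholly on the assumed ICC and cluster size and on confining clustering to Group 2. Inflation is small at the cluster sizes expected for GPs. It becomes material only if a small number of psychiatrists see most of Group 2 and the ICC is at least moderate. Clustering in Group 1 could add to it, and GPs with patients in both groups could offset it. This is a worthwhile, inexpensive improvement; it does not show that the planned analysis must fail.

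**What to change.** In the Statistics section or the analysis plan, before the data are analysed:

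- Report the one-month risk difference with a confidence interval from cluster-robust standard errors, or from GEE, with a small-sample correction.
- Cluster on the referring GP (Group 2) or declared GP (Group 1), using one identifier across both groups so that GPs with patients in both are handled correctly.
- Repeat the analysis clustered on the consulting psychiatrist in both groups, where clusters are likely to be larger.
- State the assumed ICC and cluster sizes, and report the observed number of providers and the spread of patients per provider.
- Record both identifiers. They should be obtainable from the platform and the hospital record, which the Data section names as sources, although the article does not list them as variables.

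The cost is a short addition to the text, a little more data handling, a possibly wider interval and somewhat lower power. If clustering proves negligible, the result should barely change.
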